# ETHICAL CONSIDERATIONS

## Regulation statement

The study will be conducted according to the principles of the Declaration of Helsinki (2004) and in accordance with the Medical Research Involving Human Subjects Act (WMO) and the code of conduct as accepted by The Netherlands Association for Paediatric Medicine, June 2003.

## Recruitment and consent

From all eligible patients informed consent will be procured by one of the investigators or a delegated team member (Research Coordinator). Group A patients, visiting the Emergency Department of the Erasmus Medical Centre/Sophia children’s hospital or the HAP, will have a maximum of 24 hours to decide whether or not to participate this study.

In group B parents and children receive an information leaflet on the day they attend the outpatient clinic in preparation of their surgery. A few days later they receive a phone call from a member of the study team to see if there are any questions and to make sure they have all the information they require to be well-informed. If parents and patients decide to participate, the informed consent form is signed. In practice this means healthy controls usually have up to one week to decide about participation in this trial.

The subject or legally acceptable representative should receive a copy of the signed informed consent and any other written information provided to study subjects.

## Objection by minors or incapacitated subjects

Investigators must follow standard procedures to ensure that the minor’s parents or legally acceptable representatives are able to give fully informed written consent. All local laws, rules and regulations regarding informed consent of minors must be followed. For minors, according to local legislation, one or both parents or legally acceptable representative must be informed of the study procedures and must sign the informed consent form approved for the study prior to clinical trial participation. Minors who are  12 years of age must also give their written assent.

All our subjects are children. Behaviour of all subjects will be assessed at all times during the study procedures. In accordance with the code of conduct accepted by The Netherlands Association for Paediatric Medicine (NVK), June 2001, any behaviour not within bounds of normal behaviour when confronted with situations not encountered in normal day live, will be defined as resistance or an expression of objection. The participation of these subjects will be invalidated, that is, excluded form the study according to law (WMO, art. 4, lid 2).

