## Study procedures

Visit 1:

From each patient the following samples will be obtained

- Oropharyngeal swab
- Nasopharyngeal swab
- Nasopharyngeal lavage
- Serum (blood sample of 200 microliters)

Patients from group A will have their samples taken during their visit at the Emergency Department/HAP. In those cases many of the samples are taken for diagnostic reasons anyway. Samples can usually be split for clinical (diagnostic) and research purposes. This will minimize the burden for the patients.

Patients from group B are at the day care ward for surgical treatment. The blood sample will be drawn from the vena puncture, which is conducted by the anaesthesiologist, in order to obtain iv-access for administration of anaesthetics drugs. The other samples are taken after the patient has had their anaesthetics.

Patients from both groups fill out a short questionnaire about their health (history, use of antibiotics, smoking, attendance of day care centre, etc)

Visit 2:

Group A will be asked to return for a follow-up visit, 3 tot 4 weeks after their initial visit. During this visit another blood sample will be taken and there will be another short questionnaire.

Group B will not have to return to hospital. They will be phoned by a member of the research team to check if there were any respiratory tract infections in our healthy control or his/her family since the day of surgery.

Withdrawal of individual subjects

Subjects can leave the study at any time for any reason if they wish to do so without any consequences. The investigator can decide to withdraw a subject from the study for urgent medical reasons.

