### Study design

## *Approach*

Children enrolled in the study as described under Aim I in chapter 3, may participate in the follow up study if they tested positive for *M. pneumoniae* by either real time PCR or culture in a sample taken during the first visit. The results of the tests taken during the first visit will be made available to parents and participants about one week prior to the second visit. Subsequently they will be asked to participate in the following protocol

*Definitions*

1. Children with RTI in combination with the presence of *M. pneumoniae,* as detected by either culture or real-time PCR in either the oropharyngeal swab or the nasopharyngeal lavage taken during the first visit, i.e. **group A+** or **group HAP+**. (Note: these children not necessarily suffer from disease caused by infection with *M. pneumoniae*. The gold standard for *M. pneumoniae* infection in this study is serology in combination with standard PCR.)

2. Healthy children tested positive for *M. pneumoniae* by culture or real-time PCR in either the oropharyngeal swab or the nasopharyngeal lavage taken during the first visit, i.e. **group B+**.

*Follow up protocol*

In the follow up protocol participants will be tested for the presence of *M. pneumoniae* in the nasopharynx and oropharynx once a month during a maximum period of one year or until they test negative in both tests (culture and real-time PCR) on two successive occasions. For monthly sample collections, either house-calls will be performed or participants may visit the emergency department of the Erasmus MC – Sophia, whichever is most convenient for participants at that time. If a child, participating in this study, suffers from a RTI during the follow up period, he/she will be evaluated, during daytime, by a physician specialized in pediatric infectious diseases. At all times during the follow up study, parents are free to take him/her to their own general practitioner. For emergencies parents should follow the normal procedures.

*Clinical samples*

Each month a nasopharyngeal lavage and an oropharyngeal swab will be taken and real-time PCR and culture will be performed for *M. pneumoniae* as described previously in chapter 3. Test results will be made available to the participants and their parents every month since these results determine whether the study is continued for each participant individually.

*Clinical data*

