### Study Methods

*Additional visits for follow up*

Group A+/HAP+ and B+ will be asked to return for a maximum of 12 follow-up visits after visit 1. For convenience of participants, house calls will be offered to each participant and their parents and performed by the research team. During these visits a nasopharyngeal lavage and an oropharyngeal swab will be taken and there will be additional short questionnaires.

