### Statistics

*Research question(s)*

Does the presence of *M. pneumoniae* in healthy individuals at a certain time point reflect a persistent carriage stage or merely an increasing or declining bacterial load before or after an infection?

*Analysis*

Bacterial load will be determined in samples taken from each visit. These will be used mainly in a descriptive fashion. We hypothesize that a persistent carriage stage does not exist and expect to find clearance of bacteria in all patients eventually. The number of RTI will be scored in each group. The time to clear all bacteria (defined by a negative PCR) will be determined for each individual and means will be compared between each group. The genotype of *M. pneumoniae* will be determined in every sample to compare to ‘time to clear’ and severity of infections.

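### In the carriage follow-up study, children who leave while positive or are still positive at month 12 drop out of the mean time to clear, which leans towards the stated hypothesis

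*Protocol*

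**What the plan says.** Protocol 10.3 covers every child and every procedure: "Behaviour of all subjects will be assessed at all times during the study procedures". The trigger is "any behaviour not within bounds of normal behaviour when confronted with situations not encountered in normal day live". The consequence is "The participation of these subjects will be invalidated, that is, excluded form the study according to law". The section does not say what happens to results already obtained. Separately, 7.3 lets any subject leave at any time and for any reason.

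In the follow-up study, 12.1.3 tests positive children "once a month during a maximum period of one year or until they test negative in both tests", with two successive negative occasions required to stop. Under 12.1.5 the children "will be asked to return for a maximum of 12 follow-up visits after visit 1". Each visit consists of a nasopharyngeal lavage and an oropharyngeal swab, at home or in the emergency department.

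Section 12.1.6 states the expectation: "We hypothesize that a persistent carriage stage does not exist and expect to find clearance of bacteria in all patients eventually". Clearance is defined by a negative PCR. A time to clear is to be found for each child, and group means are compared. No rule covers a child who leaves before clearing or who is still positive at the last visit. The sample size paragraph in 12.1.4 calls the study descriptive and expects 50 eligible children.

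**The concern.** The number of samplings a child faces is set by how long it carries the organism, and duration of carriage is the outcome. A child who clears at once meets two follow-up visits; a persistent carrier meets up to twelve. Any risk of loss that recurs at each visit therefore removes long carriers more often than early clearers.

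The planned summary does not correct for this. A mean over individual times to clear can use only children who have such a time. A child lost while positive has none, and neither has a child still positive at month 12. Both are the children who would speak against the hypothesis, so the result leans towards early clearance.

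**Working it through.** **The plan's own figure.** Expected eligible children: 10% positive × (500 + 500) × 1/2 = 50. This agrees with 12.1.4.

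**Inputs from the Protocol.** The fewest visits for a clearer is 2 (two successive negative occasions, 12.1.3). The maximum is 12 (12.1.5).

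**Assumptions, not in the Protocol.** q is the chance per visit that a child is excluded for objection, taken as 2%, 5% or 10%, equal for all children and independent between visits. 20% of carriers stay positive throughout (12 visits), and the rest need 3 visits. An excluded child is not counted.

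**Step 1, share of persistent carriers.** Retention over m visits is (1 − q)^m. The apparent share is 0.2(1 − q)^12 / [0.2(1 − q)^12 + 0.8(1 − q)^3].

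| q | retained, 3 visits | retained, 12 visits | apparent share (true 20%) |
|---|---|---|---|
| 2% | 94% | 78% | 17.2% |
| 5% | 86% | 54% | 13.6% |
| 10% | 73% | 28% | 8.8% |

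At q = 5% with 50 children, about 10 × 0.54 = 5.4 of 10 persistent carriers remain, against 40 × 0.857 = 34.3 of 40 clearers. If clearers need 6 visits instead of 3, the apparent shares are 18.1%, 15.5% and 11.7%.

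**Step 2, sensitivity to independence.** Exclusion over k visits is 1 − (1 − q)^k. For k = 2 against k = 12 this gives 4.0% against 21.5% (ratio 5.4) at q = 2%, 9.8% against 46.0% (4.7) at 5%, and 19.0% against 71.8% (3.8) at 10%. If the tendency to object differs between children (beta-distributed, mean 5%), the ratio is 3.6, 2.5, 1.75 and 1.2 at within-child correlations of 0.1, 0.3, 0.6 and 0.9. The direction holds throughout; the size does not.

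**Step 3, the mean, even with no objections.** Suppose 40 of 50 children are first negative at month 2 (three visits in all) and 10 are positive through month 12. The mean over children with a value is 2 months, because the 10 contribute nothing. Counting all 50 up to month 12 gives 0.8 × 2 + 0.2 × 12 = 4.0 months.

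**Step 4, what censoring does.** In the same example with objection risk q, both kinds of child reach the month 2 result with probability (1 − q)^2. A Kaplan-Meier estimate at month 2 therefore has the true mix at risk and gives 20% still positive for any q. No child clears later, so the estimate stays at 20% to month 12. This requires that results before an objection are kept, and that objecting at a given visit is unrelated to when the child would have cleared.

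**The case against.** Several points on the other side stand.

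- A reader might infer that 10.3 orders the deletion of samples already taken. It does not say so. It sits in the ethics chapter, defines no analysis set, and could mean only that procedures end. The shares in Step 1 apply to the reading in which the child no longer counts. The loss from the mean does not depend on that reading, because a child removed while positive has no time to clear either way.
- A reader might infer that long carriers are lost many times more often. That needs an objection rate and independence between visits, and the Protocol gives neither. Only behaviour outside normal bounds counts, so ordinary distress at a lavage is not a trigger. A child who has tolerated eight lavages may be unlikely to object at the ninth.
- A reader might infer that the objection rule itself is the flaw. It is presented as a legal duty, and the law and code of conduct it cites cannot be examined here. Voluntary withdrawal under 7.3 can produce the same loss. The weak point is the analysis in 12.1.6.
- The study is descriptive and small. The hypothesis concerns all children, so one retained long carrier speaks against it. With 10 persistent carriers, the chance that all are excluded is (1 − 0.9^12)^10, about 3.6%, at q = 10%, and about 0.04% at 5%. The fall from 20% to 17% at q = 2% is well inside the sampling error at n = 50: √(0.2 × 0.8/50) = 5.7 percentage points.
- A reader might extend the point to the main comparison, since for group B's swabs and lavage "The other samples are taken after the patient has had their anaesthetics", while group A is sampled at its emergency department or general practitioner visit. There, however, the samplings do not multiply with duration of carriage, and the Protocol supports no direction of bias.

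It might also be said that handling of dropouts belongs in an analysis plan. But the Protocol itself fixes the comparison of means, and that choice has no place for a child without a clearance time.

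**Conclusion.** The point holds for the analysis in 12.1.6. For any chance of loss above zero at each visit, loss rises with duration of carriage, and children without an observed clearance fall out of the mean. The bias is towards shorter carriage and so towards the stated hypothesis. Children still positive at month 12 cause the same understatement of the mean without any objection or withdrawal.

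The size cannot be derived from the Protocol. A true share of 20% appearing as about 17% to 9% rests on an assumed independent 2% to 10% risk per visit, clearers needing 3 visits, and excluded children not being counted. It is smaller if objectors show themselves early or if clearers need more visits. Long carriage would be understated but, except at high objection rates with few long carriers, seldom hidden altogether. This is a cheap improvement to a descriptive analysis; it is no defect in the protection of the child.

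**What to change.** **In 12.1.6**, replace the comparison of means with a time-to-clearance analysis, for example Kaplan-Meier curves by group. Censor any child who leaves while positive, for objection or any other reason, at the last positive sample. Censor children still positive at month 12 at that visit. Report exclusions and withdrawals by group, visit and last test result, so that a reader can judge whether leaving was related to carriage.

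**In 10.3**, leave the immediate stop and the exclusion from further procedures as they are. Add a sentence stating whether results obtained before the objection are retained, as far as law, consent and the ethics committee (METC) allow.

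**Cost:** slightly more analysis work, a few sentences of text and confirmation by the METC. No child undergoes an additional procedure. Censoring cannot recover data that must lawfully be removed; the number of such children should then be reported as a limitation.

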## Benefits and risks assessment, group relatedness

M. pneumoniae is a major cause of morbidity and mortality in children in both developing countries and Western countries. Knowledge on colonization, and host and bacterial factors contributing to progression to infection is important to optimize diagnosis and treatment, and to prevent transmission of M. pneumoniae.

Obtaining these samples is considered common clinical practice. The risks and burden are negligible.

## Compensation for injury

Not applicable

## Incentives

All participants receive a toy store voucher (€ 5,-) after completing the study procedures.

# ADMINISTRATIVE ASPECTS AND PUBLICATION

## Handling and storage of data and documents

This study will be conducted in accordance with guidelines for Good Clinical practice. All patient data and material will be stored anonymously. Confidentiality will be maintained at all times. All data will be coded with a research number. The key will only be available to members the research team (investigators and research coordinator).

Human material will be kept a maximum of 10 years. Data will be kept for the duration of the study.

## Amendments

Amendments are changes made to the study after a favourable opinion by the accredited METC has been given. All amendments will be notified to the METC that gave a favourable opinion.

Non-substantial amendments will not be notified to the accredited METC and the competent authority, but will be recorded and filed by the investigator.

## Annual progress report

The investigator will submit an annual progress report of the trial to the accredited METC. Information will be provided on the date of inclusion of the first subject, numbers of subjects included and numbers of subjects that have completed the trial, serious adverse events/ serious adverse reactions, other problems, and amendments.

## End of study report

The investigator will notify the accredited METC of the end of the study within a period of 8 weeks. The end of the study is defined as the last patient’s last visit.

In case the study is ended prematurely, the investigator will notify the accredited METC, including the reasons for the premature termination.

Within one year after the end of the study, the investigator/sponsor will submit a final study report with the results of the study, including any publications/abstracts of the study, to the accredited METC.

## Public disclosure and publication policy

Study outcomes and endpoints will be published in an international medical journal. No clinical data will be published.

# Ancillary studies

## Ancillary study 1: Follow-up study to investigate carriage.

### Rationale

Preliminary data from the original MymIC study have shown the presence of *M. pneumoniae* in the respiratory tract of healthy individuals. In addition, the actual bacterial load (determined by real-time PCR) in patients with a RTI seems to be higher than in healthy individuals. These data suggest that asymptomatic colonization with *M. pneumoniae*, defined as a single positive test for *M. pneumoniae* at a certain timepoint, exists. This now leaves room for two options: (1) presence of *M. pneumoniae* in a healthy individual is always associated with an RTI either before or after, reflecting an increasing or declining load, or (2) the presence of *M. pneumoniae* reflects a persistent carriage stage without resulting in infection. At this moment there is no evidence for either of these possibilities and very little is known about *M. pneumoniae* carriage. In this study we will address this issue by performing follow up sampling in both participants with an RTI caused by *M. pneumoniae* and healthy participants with a positive *M. pneumoniae* test (either culture or PCR). The bacterial load and genotype*,* found in these follow-up samples will be related to clinical data in a descriptive manner.

### Objective

To further elucidate the dynamics of asymptomatic colonization of *M. pneumonae* and establishing the value of a positive real-time PCR result.

### Study design

## *Approach*

Children enrolled in the study as described under Aim I in chapter 3, may participate in the follow up study if they tested positive for *M. pneumoniae* by either real time PCR or culture in a sample taken during the first visit. The results of the tests taken during the first visit will be made available to parents and participants about one week prior to the second visit. Subsequently they will be asked to participate in the following protocol

*Definitions*

1. Children with RTI in combination with the presence of *M. pneumoniae,* as detected by either culture or real-time PCR in either the oropharyngeal swab or the nasopharyngeal lavage taken during the first visit, i.e. **group A+** or **group HAP+**. (Note: these children not necessarily suffer from disease caused by infection with *M. pneumoniae*. The gold standard for *M. pneumoniae* infection in this study is serology in combination with standard PCR.)

2. Healthy children tested positive for *M. pneumoniae* by culture or real-time PCR in either the oropharyngeal swab or the nasopharyngeal lavage taken during the first visit, i.e. **group B+**.

*Follow up protocol*

In the follow up protocol participants will be tested for the presence of *M. pneumoniae* in the nasopharynx and oropharynx once a month during a maximum period of one year or until they test negative in both tests (culture and real-time PCR) on two successive occasions. For monthly sample collections, either house-calls will be performed or participants may visit the emergency department of the Erasmus MC – Sophia, whichever is most convenient for participants at that time. If a child, participating in this study, suffers from a RTI during the follow up period, he/she will be evaluated, during daytime, by a physician specialized in pediatric infectious diseases. At all times during the follow up study, parents are free to take him/her to their own general practitioner. For emergencies parents should follow the normal procedures.

*Clinical samples*

Each month a nasopharyngeal lavage and an oropharyngeal swab will be taken and real-time PCR and culture will be performed for *M. pneumoniae* as described previously in chapter 3. Test results will be made available to the participants and their parents every month since these results determine whether the study is continued for each participant individually.

*Clinical data*

Each visit, information about RTI (both participant as well as siblings and parents), use of antibiotics, hospitalization, complications and vaccinations in the previous month will be recorded in a standardized questionnaire.

*Detection of M. pneumoniae*

See Aim I, chapter 3

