All swabs will be washed out in a buffer, which allows bacterial culturing as well as total nucleic acid (DNA and RNA) purification. Material will be frozen at -80C and analyzed as a batch. Purified nucleic acids will be used in real-time PCR assays for the detection of M. pneumoniae.

M. pneumoniae will be detected and quantified using a quantitative, real-time (TaqMan®) PCR assay that has recently been developed in the Laboratory of Pediatrics by Dr. [name].

RTI by M. pneumoniae will be defined by RTI symptoms in combination with serology and/or culture positive for M. pneumoniae and/or conventional PCR for M. pneumoniae.

Aim II: To study the role of host factors (age, and bacterial and viral co-infection) on infection by M. pneumoniae

*Approach*

See aim I

*Clinical samples*

See aim I

*Clinical data*

See aim I. Virulence will be defined by disease severity (determined by hospitalization and duration of hospitalization).

*Detection of M. pneumoniae and other bacteria and viruses:*

See aim I. The other bacteria that will be investigated are S. pneumoniae, Staphylococcus aureus, Haemophilus Influenzae and Moraxella catarrhalis. These bacteria will be detected using routine, conventional bacterial culturing. In collaboration with the department of virology ([name]. [name]), the following respiratory viruses will be detected by real-time PCR: influenzaviruses, parainfluenzaviruses, rhinoviruses, respiratory syncitial virus (RSV), coronaviruses and human metapneumovirus (hMPV).

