### Study population

## *Population*

Group A+/HAP+: children, aged 0-16 years tested positive for *M. pneumoniae* in group A/HAP by culture or PCR (we expect to find 10% *M. pneumoniae* positive RTI).

Group B+: children, aged 0-16 years tested positive for *M. pneumoniae* in group B by PCR or culture (we expect to find 10% of these children to be positive by PCR).

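### The follow-up study's RTI group means infection in its rationale but any test-positive RTI child in its definitions, and time to clear is compared without separating the two

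*Protocol*

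**What the plan says.** Protocol 12.1.1 (Rationale) sets out two explanations for a positive test in a healthy child: a rising or falling load around an infection, or persistent carriage. It proposes to address them by "follow up sampling in both participants with an RTI caused by" M. pneumoniae and in healthy children who test positive.

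Protocol 12.1.3 (Definitions) builds the RTI group, A+/HAP+, differently. It takes children with an RTI and M. pneumoniae present "as detected by either culture or real-time PCR in either the oropharyngeal swab or the nasopharyngeal lavage taken during the first visit". A note adds that "these children not necessarily suffer from disease caused by infection with" M. pneumoniae, and that the gold standard for M. pneumoniae "infection in this study is serology in combination with standard PCR". The population, inclusion and exclusion text in 12.1.4 follows the test-positive rule and has no serological criterion.

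Protocol 12.1.6 (Statistics) determines time to clear for each child and says "means will be compared between each group". It also sets genotype against time to clear and against the severity of infections. It does not use the gold standard named in 12.1.3.

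The main study has another case definition. Section 3 (Aim I) defines RTI by M. pneumoniae as "RTI symptoms in combination with serology and/or culture positive for M. pneumoniae and/or conventional PCR for M. pneumoniae", and section 9, Question 1, applies a similar and/or rule. Section 9, Question 3, recognises children in group A who are positive by quantitative PCR but whose RTI has another cause, and counts them as carriers.

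**The concern.** The group named in the rationale is not the group that is enrolled and analysed. The note in 12.1.3 discloses the mixture, but no analysis step follows from it. The main study treats test-positive children with another RTI as carriers, whereas the follow-up study, whose subject is carriage, leaves them pooled with infected children.

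The stake is the reading of the comparison between A+/HAP+ and B+. If carriers with an unrelated RTI clear like healthy carriers, pooling pulls the A+/HAP+ mean towards the B+ mean. Similar clearance in the two groups could then reflect who was put in A+/HAP+ rather than how infection and carriage behave. This also touches the stated aim (12.1.2) of establishing what a positive real-time PCR means. A difference in means is distorted in this way whether it is tested or only described.

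**Working it through.** **1. The plan's own figure.** Section 4.1 plans 500 children in group A and 500 in group B. The sample size text in 12.1.4 gives about 10% positive and a start halfway through the main study.

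- 10% × (500 + 500) × 1/2 = 50, which matches the 50 stated.
- With equal group sizes and equal positivity in the remaining recruitment (assumption), about 25 are A+/HAP+ and 25 are B+.

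**2. The texts side by side.**

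| Place | Who counts as an M. pneumoniae RTI, or enters the RTI group |
| --- | --- |
| 12.1.1 | RTI caused by M. pneumoniae |
| 12.1.3 definition, 12.1.4 | Any RTI with positive culture or real-time PCR |
| 12.1.3 note | Infection requires serology together with standard PCR |
| Section 3 (Aim I), section 9 (Question 1) | RTI with any of serology, culture, conventional PCR |
| 12.1.6 | Groups as enrolled |

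The gap between 12.1.1 and the enrolled group depends on which infection definition applies. Under the and/or rule, an RTI child positive by culture or conventional PCR is already a case, so the gap is mainly children positive by real-time PCR alone. Under the rule in the 12.1.3 note, it also includes every test-positive child without serological confirmation.

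**3. Carrier share of A+/HAP+.** Let p be positivity in RTI children, i the infected proportion, and k carriage among RTI children who are not infected. Assume every infected child tests positive at visit 1. Then p = i + (1 − i)k, so i = (p − k)/(1 − k), and the carrier share is c = 1 − i/p.

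The population text in 12.1.4 expects 10% positivity in RTI children, so p = 0.10. For group B it says "we expect to find 10% of these children to be positive by PCR". The protocol gives no carriage rate specific to RTI children, so k is an assumption:

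- k = 2%: i = 0.08/0.98 = 0.0816, c = 0.18
- k = 3%: i = 0.07/0.97 = 0.0722, c = 0.28
- k = 5%: i = 0.05/0.95 = 0.0526, c = 0.47

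**4. Effect on the comparison.** The A+/HAP+ mean is (1 − c) × (infected mean) + c × (mean of carriers with another RTI). If those carriers have the same mean as B+, the expected difference between A+/HAP+ and B+ is (1 − c) times the true difference between infection and carriage. The fraction kept is 0.82, 0.72 or 0.53 for the three values of k. If those carriers do not clear like B+ children, this proportion does not apply. The protocol has no clearance data to settle it.

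**5. Size of the confirmed group after a split.** With perfect confirmation, about 25 × (1 − c) children remain: 20, 18 or 13.

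**The case against.** The strongest reply is that the protocol conceals nothing and claims little. The mixture is stated in the definition itself. 12.1.1 promises sampling in both groups and a descriptive account, and does not promise a formal contrast with an infection arm. The main question concerns healthy positives, and monthly loads and RTI questionnaires in B+ address it within each child. The comparison of means is one sentence in a study that 12.1.4 calls merely descriptive. This stands, and it limits the point to the comparison of A+/HAP+ with B+ and to what is concluded about a positive PCR. It does not remove the conflict between 12.1.1 and 12.1.3, and a descriptive mean is blurred by mixing just as a tested one is.

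It can also be said that subgrouping by serology belongs in an analysis plan. But this protocol itself fixes the groups and the comparison, and they disagree with its rationale.

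Three stronger readings are tempting and are not supported:

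- **All of A+/HAP+ could be carriers.** A reader might infer this by equating the 10% expected in RTI children with the 10% in healthy children. That takes two rounded expectations as exact. It would leave no M. pneumoniae infections in group A, which sits badly with the infections assumed in section 4.4 and with the higher load in RTI patients reported in 12.1.1.
- **A stated loss of power.** No test, alpha, SD or effect size is given for time to clear, so any power figure would rest wholly on assumed values.
- **Every unconfirmed child is a carrier.** Section 1 says that antibody detection has suboptimal sensitivity and specificity, so some unconfirmed children will be truly infected.

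**Conclusion.** The inconsistency is real and nothing in 12.1.3 to 12.1.6 resolves it. As written, the A+/HAP+ mean time to clear pools infected children with carriers who have another RTI. Beneath this lies a second conflict: the 12.1.3 note requires serology together with standard PCR, while sections 3 and 9 accept any one of several tests.

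The size is unknown. A carrier share of about 18% to 47% follows from the protocol's 10% positivity and an assumed 2% to 5% carriage among RTI children. The blurring of the difference in proportion to that share further assumes that these carriers clear like B+ children. The consequence is confined to one descriptive comparison and its interpretation. It does not undermine the within-child follow-up of B+. It is still worth correcting, because the correction is specific and cheap.

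**What to change.** Leave the entry criteria as they are, and change the following.

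1. State which infection definition governs the follow-up study, by reconciling the 12.1.3 note with section 3 (Aim I) and section 9 (Question 1).
2. In 12.1.6, report load and time to clear separately for (a) A+/HAP+ confirmed by that definition, (b) A+/HAP+ not confirmed, and (c) B+. Take (a) versus (c) as the contrast of infection with carriage, and show pooled A+/HAP+ versus B+ alongside.
3. Label (b) as unconfirmed, not as carriage, because serology is imperfect.
4. Say what severity of infections means in the genotype comparison. If it is the RTI at enrolment, report it for (a).
5. Align the wording of 12.1.1 with these groups.

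The cost is wording. A second serum sample is already planned in group A (sections 3 and 7.3), and conventional PCR is already part of the main case definition, so no visit or sample is added. There are two drawbacks. The confirmed group is smaller, perhaps about half of 25 at the upper end of the range above. And B+ has no second serum sample, so healthy positives cannot be classified in the same way; the report should say so.
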